### Statistical analysis

All analyses will be conducted according to the intention-to-treat principle and will be performed before breaking the randomization code. Baseline characteristics are presented and compared clinically. Primary and secondary endpoints will be analyzed using linear regression for continuous variables and logistic regression for binary outcome measures, including heart failure etiology as a variable in the model. Multivariate regression analysis will be reported for absolute change in LVEF including baseline LVEF, heart failure etiology, sex, and baseline QRS width as covariates. Predictors of missing outcome values will be identified by comparing baseline characteristics and will be included in a multivariate regression model for sensitivity analysis. Intraclass correlation coefficients are computed to assess intraobserver and interobserver agreement for the echocardiographic parameters included in the primary endpoint: LVEF, LVEDV, LVESV assessed for 20 echocardiograms. A two-sided *P* value < 0.05 is considered significant.

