### Randomization and blinding procedures

After baseline clinical evaluation and pre-implant imaging, patients are allocated either to the intervention or the control group. Study data are recorded in a web-based case record form (CRF) with logging of all data entries. The CRF is also used for randomization using computerized permuted blocks of different sizes. Randomization is stratified according to ischemic or non-ischemic heart failure etiology. An external data manager is responsible for the CRF and has programmed a computerized random-number generator.

Patients and physicians responsible for enrollment, baseline and follow-up clinical evaluation, including imaging acquisition, are blinded to the allocated treatment. Information about randomization is available only to the physician performing the implant. Data related to the device implantation, post-implant device-tests, and optimization are collected and entered into the CRF by the physicians performing the implantation and the dedicated research nurses, to ensure blinding of the investigator collecting clinical and imaging data. Information on the randomization code will be available when all patients have completed the 6MFU and all statistical analyses have been performed.

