### Endpoints

The primary endpoint is absolute change in left ventricular ejection fraction (LVEF) from baseline to 6MFU measured by 2D echocardiography. Secondary outcomes include relative percentage reduction in LV end-systolic volume (LVESV) and a combined clinical outcome measure of response to CRT at 6MFU defined as the patient being alive, not hospitalized for heart failure, and experiencing an improvement in NYHA functional class or/and > 10% increase in 6MWT [17]. Hospitalization for heart failure is defined as admission to hospital for more than 24 h with symptoms of congestive heart failure and need for intensified drug treatment for heart failure. Other secondary outcome measures include:All-cause mortality.Hospitalization for heart failure.Implantation procedure time.Procedural radiation exposure.Device-related complications.Indices of dyssynchrony and association between dyssynchrony, LV lead placement, and response to CRT.Changes in QoL, NYHA functional class, 6MWT, N-terminal prohormone of brain natriuretic peptide (Nt Pro-BNP), QRS duration, LV end-diastolic volume (LVEDV), LVESV, LVEF, mechanical dyssynchrony, and LV lead parameters (pacing threshold, sensing value, impedance).

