### Sample size

We hypothesize that the intervention group strategy will result in an excess increase in LVEF of 4% compared with the strategy used in the control group, where an 8% increase in LVEF is expected [9]. To identify this absolute increase in LVEF of 12% in the intervention group and to achieve statistical power of 80%, the study will need a sample size of 98 patients, given a standard deviation (SD) of 7% in both groups, and a two-sided alpha value of 0.05. To achieve statistical power of 80% for the secondary endpoint of relative reduction in LVESV a sample size of 116 patients is needed, when assuming a 33% reduction in the control group and a 45% reduction in the intervention group (expected SD of 23% in both groups and given a two-sided alpha value of 0.05%). To achieve statistical power of > 80% with a margin of non-inferiority of 20% for the secondary endpoint of clinical response to CRT (assuming a 75% clinical response rate in the control group) we will need a sample size of 116 patients (given a two-sided alpha value of 0.05%). Taking into consideration expected loss to follow up in approximately 5% of patients, 122 patients are included.

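### The model attached to the primary endpoint adjusts only for etiology; baseline LVEF should be in the one model that decides the trial

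*Protocol article*

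**What the plan says.** The Endpoints section defines the outcome: "The primary endpoint is absolute change in left ventricular ejection fraction (LVEF) from baseline to 6MFU measured by 2D echocardiography". The Statistical analysis section then gives two models for it.

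- The first covers all endpoints: "Primary and secondary endpoints will be analyzed using linear regression for continuous variables and logistic regression for binary outcome measures, including heart failure etiology". Etiology is the only covariate named. It is also the only stratification factor: "Randomization is stratified according to ischemic or non-ischemic heart failure etiology".
- The next sentence adds: "Multivariate regression analysis will be reported for absolute change in LVEF including baseline LVEF, heart failure etiology, sex, and baseline QRS width as covariates".

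The second model is not called primary, supportive or sensitivity. The section uses the sensitivity label only for the missing-data model. The 5% significance threshold that closes the section is not tied to either model. No baseline value is named as a covariate for any other continuous change outcome.

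**The concern.** Baseline LVEF is measured in every patient and is usually related to the change from baseline, because low starting values tend to rise and high ones to fall. A change score analysed without its baseline keeps that variation in the error term. It also lets a chance difference in baseline LVEF between arms pass into the estimated treatment effect. Stratifying on etiology alone does not balance baseline LVEF.

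The sponsor evidently regards baseline LVEF as worth adjusting for, since it appears in the second model. It is absent from the model to which the primary endpoint is attached. What is at stake is precision that would cost nothing to recover and, to a lesser degree, certainty about which P value decides.

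**Working it through.** **Inputs from the Sample size section.** The difference is 4 points ("excess increase in LVEF of 4% compared with the strategy used in the control group, where an 8% increase in LVEF is expected"). The variability and error rate are "given a standard deviation (SD) of 7% in both groups, and a two-sided alpha value of 0.05". The stated result is "to achieve statistical power of 80%, the study will need a sample size of 98 patients". With 122 enrolled and about 5% lost, 122 × 0.95 ≈ 116 are evaluable, or 58 per arm at 1:1 allocation.

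**The plan's own figure.** n per arm = 2 × (1.960 + 0.842)² × 7² / 4² = 48.1, rounded up to 49, so 98 in total. The stated figure reproduces, and it contains no reduction for baseline adjustment.

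**Power without baseline LVEF.** At 58 per arm the standard error is 7 × √(2/58) = 1.30. The t-test gives 86.2% power and the normal approximation 86.8%. At 49 per arm the normal approximation gives 80.7%. The etiology-only model therefore stays above the planned 80%.

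**Power with baseline LVEF.** Let r be the size of the correlation between baseline LVEF and its change. The documents do not give r, so a range is assumed. The residual SD becomes 7 × √(1 − r²).

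| Assumed r | Variance removed (r²) | Residual SD | t-test power, 58 per arm | 95% CI half-width (points) | Total N for 80% power |
|---|---|---|---|---|---|
| 0 | 0% | 7.00 | 86.2% | 2.55 | 98 |
| 0.2 | 4% | 6.86 | 87.6% | 2.50 | 94 |
| 0.3 | 9% | 6.68 | 89.2% | 2.43 | 88 |
| 0.4 | 16% | 6.42 | 91.5% | 2.34 | 82 |
| 0.5 | 25% | 6.06 | 94.1% | 2.21 | 74 |

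In patient numbers the gain is 1/(1 − r²) − 1: 4% more patients at r = 0.2 (1/0.96) and 33% more at r = 0.5 (1/0.75).

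**Chance imbalance.** The slope of change on baseline is r × 7 / SD(baseline) in size. The standard error of the baseline difference between arms is SD(baseline) × √(2/58). In their product the baseline SD cancels, so the shift at the edge of the 95% range is 1.96 × r × 7 × √(2/58) = 2.55 × r:

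- r = 0.2: 0.5 points
- r = 0.3: 0.8 points
- r = 0.5: 1.3 points

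This is the same variance component as the precision loss, seen within a single trial. The two should not be added together.

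**If the decisive model were left open.** Trials of 116 patients were simulated, 10,000 per scenario, and both models were fitted to each. Sex and QRS width were treated as unrelated to outcome.

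| Assumed r | Models disagree on significance, 4-point effect | Type I error if either P < 0.05 counts as success |
|---|---|---|
| 0 | about 3% | 5.9% |
| 0.3 | about 6% | 6.5% |
| 0.5 | about 10% | 7.8% |

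Either model alone held about 5%. At r = 0 the larger model had about one percentage point less power than the etiology-only model (84.8% against 85.7%), so the extra covariates cost little when they do not help.

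**The case against.** The strongest reply is that nothing here is an error. The comparison is randomized, the change-score estimate is unbiased on average, and regression to the mean is expected equally in both arms. The sample size was calculated on that basis and reproduces. Power exceeds the target without adjustment. The size of any gain rests on a correlation that the documents do not give, and the entry limit of LVEF ≤ 35% narrows the baseline spread and may weaken it. All of this stands. It makes the point one of efficiency, and it does not show that leaving baseline LVEF out of the deciding model has any advantage.

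A reader might infer that the plan has two competing answers to its primary question. The text does not support that. The first sentence attaches the primary endpoint to the etiology-only model, and the natural reading of the second is an additional analysis. The missing element is an explicit label, which a separate SAP, not shown, may supply. The two harms are also alternatives: precision is lost if the etiology-only model decides, and P values compete only if neither model does. Both models are announced in advance, and the article places all analyses before the code is broken, which hides the direction of any difference. It would not hide which model gave the smaller P value, so a label still has some use.

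A reader might also want LVESV analysed on a log scale. The declared endpoint is a relative percentage reduction, and the trial was sized on that scale. A log scale would replace a declared endpoint without showing that anything is wrong with it.

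**Conclusion.** The point holds as one of efficiency and clarity. As printed, the model attached to the primary endpoint leaves out baseline LVEF, and the model that includes it has no stated role. The etiology-only analysis is valid and has about 86% power at 58 per arm.

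If r is between 0.2 and 0.5, adjustment would cut residual variance by 4 to 25% and lift power to about 88 to 94%. An extreme chance imbalance would move the unadjusted estimate by about 0.5 to 1.3 points against a 4-point target, and typical imbalances would move it less. With r near zero there is nothing to gain. These figures rest on the plan's SD of 7, 116 evaluable patients and the assumed range of r. The documents do not support a stronger claim that the trial is underpowered, biased on average or without a main analysis.

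**What to change.** Name one decisive analysis for the primary endpoint: linear regression of LVEF change (or of 6-month LVEF) on arm, etiology and baseline LVEF. Sex and baseline QRS width may stay, as they are already listed. Label the etiology-only model supportive. That also settles which of the two P values decides.

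For each other continuous change outcome, add its own baseline value as a covariate and keep the declared scale. For LVESV this means the percentage reduction with baseline LVESV in the model.

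The choice must be recorded before the randomization code is broken. Because the article schedules the analyses before that event, it should in practice be recorded before any outcome comparison of the coded groups is run. The cost is a sentence or two in the analysis plan. The baseline values belong to measurements already scheduled, and the sample size does not change.

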### Study population

Patients are recruited at a tertiary referral center (Department of Cardiology, Aarhus University Hospital, Denmark). Consecutive patients referred to CRT-pacemaker (CRT-P) or CRT-defibrillator (CRT-D) and meeting the inclusion and exclusion criteria are eligible for study participation (Table 1).

**Table 1 Tab1:** Inclusion and exclusion criteria

Inclusion criteria	
Symptomatic heart failure (NYHA class II–IV despite OMT)	
ECG with LBBB according to the Strauss criteria [37] or indwelling single or dual chamber pacemaker and a paced QRS ≥ 180 ms	
LVEF ≤ 35%	
Age ≥ 40 years	
Written informed consent	
Exclusion criteria	
Expected lifetime < 6 months	
Expected cardiac surgery within the next 6 months	
Recent (< 3 months) myocardial infarction or CABG	
Pregnant or lactating	

*NYHA* New York Heart Association, *OMT* optimal therapy for the individual patient at the time of referral for cardiac resynchronization therapy, *ECG* electrocardiogram, *LBBB* left bundle branch block, *LVEF* left ventricular ejection fraction, *CABG* coronary artery bypass graft

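### Change in NYHA class would be analysed without baseline class, which costs precision on a minor secondary outcome but does not bias the comparison

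*Protocol article*

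**What the plan says.** The Endpoints section lists, among the other secondary outcome measures, "Changes in QoL, NYHA functional class, 6MWT" and several further changes from baseline. NYHA class appears a second time in the combined clinical response, where one route to response is "experiencing an improvement in NYHA functional class or/and > 10% increase in 6MWT"; there it is used as a yes/no item.

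Table 1 under Study population admits patients with "Symptomatic heart failure (NYHA class II–IV despite OMT".

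The Statistical analysis section says that primary and secondary endpoints will be analysed by "linear regression for continuous variables and logistic regression for binary outcome measures, including heart failure etiology as a variable in the model". It adds one model with baseline values: "Multivariate regression analysis will be reported for absolute change in LVEF including baseline LVEF, heart failure etiology, sex, and baseline QRS width as covariates". A two-sided P "value < 0.05 is considered significant". No model is assigned by name to change in NYHA class, and baseline NYHA class is in no stated model.

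The Sample size section covers LVEF, LVESV and clinical response. It claims no power for change in NYHA class.

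**The concern.** NYHA class is an ordered scale whose best value is class I. A patient entering in class II can improve by one step at most, in class III by two and in class IV by three. A change score, or a flag for any improvement, therefore carries variation that comes from entry class and has nothing to do with treatment. The baseline visit already records entry class, so the model could remove that variation at no cost.

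The stated rule has a slot for continuous variables and a slot for binary ones, each with etiology as the only named covariate. An analyst who applies it literally to NYHA change would either treat the steps as an interval score or collapse them to improved versus not improved, in both cases without baseline class. At stake is the precision of one functional outcome in a trial that, by its own account under Choice of endpoint, is not powered for survival or heart failure hospitalization.

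**Working it through.** **The plan's own figures.** The plan has no figure for NYHA change, so the first step is the number of evaluable patients. Per arm, n = 2(1.96 + 0.842)² × SD² / difference².
- LVEF: an "excess increase in LVEF of 4% compared with the strategy used in the control group", "given a standard deviation (SD) of 7% in both groups, and a two-sided alpha value of 0.05". 2 × 7.85 × 49 / 16 = 48.1, so 49 per arm and 98 in total, as stated.
- LVESV: difference 12, SD 23, alpha 0.05. 2 × 7.85 × 529 / 144 = 57.7, so 58 per arm and 116 in total, as stated.
- Loss to follow-up: 116 × 1.05 = 121.8, which gives the 122 enrolled.

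The NYHA comparison therefore has about 116 patients, 58 per arm.

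**Assumptions, none of them from the documents.** Six-month class was simulated from

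logit P(class ≤ k) = θ_k + ln(OR) × arm − b × (entry class − 2) − 0.4 × etiology

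with entry mix II/III/IV of 50/45/5% or 30/60/10%, slope b of 0.7, 1.5 or 2.5 per class, etiology split 50/50, common odds ratio 1, 2 or 2.75, two-sided 0.05, and 3,000 trials per setting. The simulation standard error is at most √(0.5 × 0.5 / 3000) = 0.9 points.

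**Power (%), every model including arm and etiology:**

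| Entry mix, slope | OR | Linear, change | Linear + baseline | Logistic, improved | Logistic + baseline | Proportional odds, 6-month class + baseline |
|---|---|---|---|---|---|---|
| 50/45/5, 1.5 | 2.75 | 73.3 | 78.5 | 69.6 | 72.6 | 80.4 |
| 30/60/10, 1.5 | 2 | 42.5 | 47.4 | 38.0 | 41.1 | 48.6 |
| 30/60/10, 1.5 | 2.75 | 73.8 | 79.7 | 68.0 | 71.5 | 81.1 |
| 50/45/5, 0.7 | 2 | 36.9 | 46.7 | 31.4 | 36.8 | 48.2 |
| 50/45/5, 0.7 | 2.75 | 63.6 | 79.3 | 55.5 | 64.8 | 80.4 |
| 50/45/5, 2.5 | 2 | 42.7 | 44.2 | 41.0 | 42.3 | 46.0 |
| 50/45/5, 2.5 | 2.75 | 74.4 | 76.9 | 71.3 | 72.9 | 78.4 |

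**Size of the loss against the last column.**
- Linear on change: from 46.0 − 42.7 = 3.3 to 80.4 − 63.6 = 16.8 points.
- Logistic on improvement: from 46.0 − 41.0 = 5.0 to 80.4 − 55.5 = 24.9 points.

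**Where the loss comes from.**
- Linear: in the worst row, adding baseline class recovers 79.3 − 63.6 = 15.7 of the 16.8 points. In every row it brings linear regression within 1 to 2 points of proportional odds. Only where the total loss is about 3 to 4 points (slope 2.5) is that remainder a sizeable share of it.
- Logistic: adding baseline class recovers 1 to 9 points and leaves 4 to 16. Most of this loss is therefore due to collapsing the scale.
- Proportional odds without baseline class is no remedy. Applied to change, it gains only 0 to 2 points over linear regression. Applied to 6-month class, it can do much worse than linear on change (59.4% against 74.4% at slope 2.5 and OR 2.75).

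**In patients.** In the first row's setting, linear regression of change reaches 78.0% at 130 patients and 81.8% at 140, so about 135 are needed for 80%. Logistic regression of improvement reaches 80.0% at 150. The baseline-adjusted ordinal model gets there with 116.

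**Checks.** Type I error was 4.7 to 6.0% for all models. In three settings that break proportional odds, the adjusted ordinal model had 25%, 30% and 59% power, against 21%, 26% and 51% for linear on change and 23%, 20% and 50% for logistic. Linear with baseline class was level with it in the second of these (30.4% against 29.7%). A second simulation at 116 patients and OR 2.75 gave 68–76% for linear on change, 60–75% for logistic, 80–82% for linear with baseline and 81–83% for proportional odds with baseline.

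**The case against.** The strongest objection is that the text does not prescribe the weak analysis. It assigns one model to continuous variables and another to binary ones. NYHA change is strictly neither, so its model is left open, and a condensed article may leave that to a full protocol or analysis plan that is not shown. This stands in part. A reader might infer that the plan permits nothing but linear or logistic regression for NYHA change; the words do not say so. What remains is that the section states the approach and the covariate for secondary endpoints in general, and reserves baseline adjustment for LVEF. Someone following it as written would leave entry class out.

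A reader might also infer that the lack of a proportional-odds model is the fault. Against linear regression this is not supported, since adding baseline class closes nearly the whole gap. Model form matters materially only if the outcome is dichotomised, and the article does not say that it will be outside the combined response. For that combined endpoint logistic regression is suitable.

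A third inference would be that starting class is confounded with treatment. Allocation is randomised 1:1, so entry class is balanced in expectation, and type I error was close to nominal without it.

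Finally, NYHA change is one of many secondary outcomes, carries no power claim, and sits beside walk test and quality of life as functional measures. The article itself describes its findings as hypothesis-generating. All of this stands and keeps the point minor.

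**Conclusion.** The point holds as a worthwhile refinement and is not an error in the plan. Analysing change in NYHA class without entry class wastes information already collected. With about 116 patients and odds ratios of 2 to 2.75, the cost is roughly 3 to 17 power points for linear regression of change and 5 to 25 points for logistic regression of improvement.

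Those ranges depend on assumed entry mixes, slopes and treatment effects. Outside proportional odds the gap was as small as 2 points against logistic and 3 to 4 against linear. The direction was the same in every setting with a true effect, but no single figure should be quoted as this trial's loss.

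**What to change.** In the Statistical analysis section, state that NYHA class will be analysed with arm, etiology and baseline NYHA class in the model. The preferred form is proportional-odds regression of 6-month class, reporting the common odds ratio with its 95% confidence interval, a table of 6-month class by arm, and a prespecified rule for patients who die before 6 months. Linear regression with baseline class is an acceptable alternative; with baseline in the model, its treatment coefficient is the same whether the outcome is change or 6-month class. Baseline class must be kept whichever form is chosen. Use improved versus not improved only inside the combined clinical response.

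The cost is a few lines of wording and no new data. The small downside is reliance on the proportional-odds assumption. The class-by-arm table lets readers judge it, though only roughly if few patients are in class IV.

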To clarify the potential value of an electrically guided strategy for optimizing CRT response, we designed a prospective, double-blinded, randomized trial comparing an electrically guided CRT strategy with an imaging-guided approach. We hypothesize that an electrically guided CRT strategy improves CRT response by optimal electrical resynchronization targeting LV lead placement towards the region with the latest electrical activation combined with VVd optimization to achieve the narrowest biventricular paced QRS. The aim of the present study is to investigate if this strategy of optimal electrical resynchronization causes an excess improvement in LV ejection fraction (LVEF) as compared with an imaging-guided strategy positioning the LV lead according to the latest mechanically activated non-scarred myocardial segment.

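### Clinical response is powered as non-inferiority with a 20% margin, but the only stated analysis and criterion is a two-sided difference test that does not assess that margin

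*Protocol article*

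**What the plan says.** All references are to the protocol article.

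- **Sample size.** Clinical response at 6 months is sized "with a margin of non-inferiority of 20% for the secondary endpoint of clinical response to CRT". Control response is taken as 75%. The required number is 116, at a power above 80% and a two-sided alpha printed as 0.05%. The scale of the margin (absolute or relative) and the intervention response rate are not given.
- **Statistical analysis.** One sentence covers the primary and all secondary endpoints: linear regression for continuous outcomes and "logistic regression for binary outcome measures, including heart failure etiology as a variable in the model". The only success criterion is a two-sided P value below 0.05. The section mentions no margin, risk difference, confidence limit or non-inferiority rule.
- **Endpoints.** Clinical response is defined as a combined binary outcome and is not labelled a non-inferiority endpoint.

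**The concern.** The sample size asks whether response under electrical guidance could be worse than under imaging guidance by as much as the margin. The P value of a treatment term in a logistic model asks whether the odds ratio differs from 1. A non-significant result on the second question does not answer the first, in either direction.

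The article is not merely brief here. It fixes a model and a criterion for every binary secondary endpoint, and for this one they address a different hypothesis from the one powered. Followed literally, the trial would have no rule for deciding non-inferiority, and the interval level that decides a borderline result would be open to choice after the data are seen.

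**Working it through.** **Inputs.** From the article: control response 0.75, margin 0.20, power 0.80, 1:1 allocation, 116 patients, two-sided alpha 0.05, about 5% loss. Assumed: intervention response 0.75 (no true difference), since the article gives none.

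**1. Reproduce 116.** For a risk difference with equal true rates, n per arm = 2p(1-p)(z_alpha + z_power)² / margin².

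- One-sided 0.05: 0.375 × (1.645 + 0.842)² / 0.04 = 57.96, so 58 per arm, **116** in total. Exact match.
- One-sided 0.025, equivalent to two-sided 0.05: 0.375 × (1.960 + 0.842)² / 0.04 = 73.58, so 74 per arm, **148** in total.
- Margin read as relative (20% of 75%, or 15 points): 208 (one-sided 0.05) or 262 (one-sided 0.025).
- Alpha taken literally as 0.05%: 322 or 352.

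Of these readings, only 20 absolute points at one-sided 0.05 gives 116. The printed 0.05% is evidently a typing error. It also stands beside the LVESV figure, which is 116 at two-sided 0.05 and would be 276 at 0.05%.

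**2. Power with 116 evaluable patients.** SE = √(0.375/58) = 0.0804, and 0.20/0.0804 = 2.487.

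- One-sided 0.05 (90% interval): Φ(2.487 - 1.645) = **80.0%**
- One-sided 0.025 (95% interval): Φ(2.487 - 1.960) = **70.1%**; with all 122 evaluable, 72.3%

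Over a range of assumed intervention rates at one-sided 0.025 and 58 per arm: 70% gives 44%, 75% gives 70%, 78% gives 83%, 80% gives 90%, 85% gives 98%.

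**3. Does the stated criterion decide the margin?** Unadjusted, 58 per arm, control 44/58. P is for the log odds ratio. RD is the risk difference (intervention minus control) with Wald limits, in points.

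| Intervention responders | P | RD | 95% CI | 90% lower limit |
|---|---|---|---|---|
| 44 | 1.00 | 0.0 | -15.6 to +15.6 | -13.1 |
| 41 | 0.53 | -5.2 | -21.3 to +10.9 | -18.7 |
| 36 | 0.11 | -13.8 | -30.4 to +2.9 | -27.8 |

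The 90% limits use the same standard errors with 1.645: 0 - 1.645 × 7.95, -5.17 - 1.645 × 8.20 and -13.79 - 1.645 × 8.49. All three rows are non-significant. The first is non-inferior, the third is not, and the second depends wholly on an interval level that the article does not state.

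**4. Could the margin be read on the odds-ratio scale?** Twenty points below 75% is (0.55/0.45)/(0.75/0.25) = 0.407. The same 20 points correspond to 0.429 at 70% control response, 0.375 at 80%, 0.444 at 60% and 0.259 at 90%. Holding 0.407 fixed would permit a deficit of 22.1 points at 60% but 11.4 points at 90%. The log-odds SE at 58 per arm is √[2(1/43.5 + 1/14.5)] = 0.429, so power against 0.407 is Φ(0.898/0.429 - 1.960), about 55%, or 67% at one-sided 0.05. Converting the margin is not a neutral substitute.

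**5. Can the stated model supply a valid test?** Yes. In a simulation with 116 patients, assumed etiology-stratum rates of 70% and 80% and no treatment effect, a risk difference standardised from the logistic model had its 95% lower limit above -20 points in about 72% of 2,000 runs, in line with step 2.

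**The case against.** The strongest reply is that the article names a model, not an estimand. It does not say that the odds ratio is the effect measure for this endpoint, and a two-sided 5% level is compatible with a 95% interval rule. The decision rule may sit in a fuller plan that is not shown. Part of this stands: it would be wrong to infer that logistic regression cannot test the margin, and step 5 shows that it can. But the article does state a criterion for all secondary endpoints, and that criterion does not address the powered hypothesis. That goes beyond omitted detail.

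Three stronger readings are tempting, and the article does not support them.

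- **That intention-to-treat invalidates the comparison.** "All analyses will be conducted according to the intention-to-treat principle" does not prevent testing a margin. Both strategies have fallback built in: pacing-threshold and diaphragmatic-stimulation conditions in one arm, ranked target veins in the other. A lead away from the first-choice site may therefore still follow its allocated strategy. No deviation rate is given from which to judge dilution.
- **That the Background contradicts the design.** "We hypothesize that an electrically guided CRT strategy improves CRT response" is a general hypothesis, and the aim stated with it concerns LVEF. Superiority on LVEF with non-inferiority on a secondary clinical outcome is coherent, especially as the Discussion presents the electrical strategy as simpler than an already effective comparator.
- **That a non-significant odds ratio will be reported as non-inferiority.** Nothing in the article says so. If it were, a true 55% versus 75% would be non-significant about 38% of the time at 58 per arm. That is a reason to state the rule, not evidence of intent.

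**Conclusion.** The point holds as a mismatch between the design and the stated analysis of one secondary endpoint. The stated P < 0.05 rule does not assess the 20% margin, and the sample size and the stated alpha disagree: 116 gives 80.0% power at one-sided 0.05 and 70.1% at the two-sided 0.05 that the text claims, where 148 evaluable patients would be needed.

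Two assumptions carry these figures. The absolute scale of the margin is inferred, because among the readings tried only it reproduces 116. The equal 75% response rates are assumed; an intervention rate of about 78% or more would restore 80% power at the stricter level.

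The reach is limited. The primary LVEF comparison is untouched. The enrolled total also stands without this endpoint, since LVESV needs 116 on its own and 116 × 1.05 = 121.8, rounded to 122.

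**What to change.** Before the randomization code is broken:

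1. State that clinical response is analysed as an etiology-adjusted risk difference with a confidence interval, either stratified (for example Mantel-Haenszel weights) or standardised from the logistic model already named. The odds ratio can still be reported.
2. State that non-inferiority is declared only if the lower confidence limit is above -20 percentage points, and say explicitly that the margin is absolute.
3. State the interval level and reconcile it with the Sample size section. Either keep two-sided 0.05 (95% interval) and restate power as about 70% under equal 75% rates, or declare one-sided 0.05 (90% interval) openly and keep 80%. Give the assumed intervention rate in either case.
4. Correct the alpha printed as 0.05% for both secondary endpoints.

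A supportive analysis in patients implanted according to their allocated strategy is optional. It should not be a condition for the claim: the subset is formed after randomization and would lower power further.

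The cost is a few sentences and a few lines of code, with no new data. The real price is candour about power, because the article reports that enrolment ended on 13 December 2017 and 148 evaluable patients cannot come from the 122 planned.
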